## Abstract

**Background/Objectives:** This study aims to evaluate the effectiveness of binaural beats (BB) on the autonomic nervous system (ANS), kinesiophobia of reinjury and fitness biomarkers in professional athletes with chronic musculoskeletal injuries. **Methods**: A total of 54 athletes aged 18–25 years, engaged in open-skill sports and experiencing chronic lower-limb injuries for over three months, will be recruited. They will be randomly assigned to one of three groups: an intervention group, a placebo group, and a control group. All athletes will undergo a 15 min auditory intervention five times per week for four weeks. The intervention group will listen to BB embedded in music at high beta and gamma frequencies (30–100 Hz) with guided instructions. The placebo group will receive placebo BB within the same music framework, while the control group will listen only to the music background. Assessments will be conducted at baseline, immediately post-intervention, and at a 4-week follow-up. The primary outcomes will be kinesiophobia of reinjury, ANS function, and heart rate variability (HRV), assessed using the Tampa Scale of Kinesiophobia (TSK-17), Sympathetic Skin Response (SSR), and HRV analysis, respectively. Secondary outcomes will include sport-related anxiety and pain beliefs, assessed using the Sport Competition Anxiety Test (SCAT-15) and the Pain Beliefs and Perceptions Inventory (PBPI-16), respectively; handgrip strength, assessed using the Hand Grip Test; and fitness-related biomarkers, including maximal oxygen uptake (VO_2_max) and blood lactate concentration. **Conclusions**: These findings may provide evidence supporting BB as a complementary, non-invasive intervention to enhance psychological and physiological rehabilitation in injured athletes. Ethics and Dissemination: The study has received ethical approval and is registered on ClinicalTrials.gov. Findings will be disseminated through peer-reviewed publications, conferences, and academic presentations.

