## 2. Materials and Methods

### 2.1. Participants

A total of 54 professional male and female athletes aged 18–25 years will be recruited from collaborating sports clubs located in the Attica region of Greece. Eligible participants will be athletes participating in open-skill sports, including football, basketball, volleyball, and handball, who have sustained at least one chronic lower-limb musculoskeletal injury lasting more than three months. Recruitment will be conducted in collaboration with team coaches and sports medicine professionals affiliated with these clubs. Participants will be randomly assigned in a 1:1:1 ratio to one of three groups: the experimental group, the placebo group, or the control group (*n* = 18 per group). Randomization will be performed using a computer-generated random allocation sequence by an independent researcher who is not involved in participant recruitment, outcome assessment, or statistical analysis. Allocation concealment will be ensured using sequentially numbered, opaque, sealed envelopes. Participants, outcome assessors, and statisticians will remain blinded to group allocation throughout the study.

Sample size was calculated using G*Power software (version 3.1.9.7; Heinrich Heine University Düsseldorf, Düsseldorf, Germany) [47]. The calculation was based on a mixed-design repeated-measures ANOVA with three groups (experimental, placebo, and control) and three measurement time points (baseline, post-intervention, and four-week follow-up). Assuming a medium effect size (f = 0.25), an alpha level of 0.05, statistical power of 0.95 and equal allocation across groups, the minimum required sample size was estimated at 48 participants. To account for an anticipated dropout rate of approximately 10%, the final target sample size was set at 54 participants, with 18 participants allocated to each group. A medium effect size of Cohen’s f = 0.25 was selected as a realistic estimate for a non-invasive psychophysiological intervention (BB) targeting psychological and Performance outcomes. This estimate was considered appropriate because previous intervention studies examining kinesiophobia and rehabilitation-related outcomes in athletes with lower-limb injuries have reported comparable sample sizes (33–51 athletes) and medium effect estimates (0.25–0.40) [48,49,50].

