### 2.2. Procedures

This double-blind randomized controlled trial will investigate the effects of binaural beats on biopsychological outcomes in professional athletes with a history of chronic lower-limb musculoskeletal injuries. The study will be conducted in three phases: baseline (pre-intervention), immediately after the four-week intervention, and four weeks after completion of the intervention. Outcome measures will include self-report questionnaires assessing kinesiophobia, sport-related anxiety, and pain beliefs; physiological assessments of autonomic nervous system (ANS) function; handgrip strength; and fitness-related biomarkers, including maximal oxygen uptake (VO_2_max), blood lactate concentration, and heart rate variability (HRV). All athletes will complete a four-week standardized binaural beats music-based intervention incorporated into the warm-up phase prior to each training session and official game. The BB intervention will be administered 5 times per week (pre-training and pre-game), resulting in a total of 20 sessions. Each session will consist of 15 min of music listening (Figure 1).

Prior to initiating the intervention, athletes will receive detailed oral and written information regarding the study aims and assessment procedures from licensed physiotherapists with five years of clinical research experience. Data collection will include both subjective and objective measures and will be conducted at three time points: baseline (pre-intervention), immediately post-intervention, and four weeks after the completion of the intervention. Written informed consent will be obtained from all participants before enrollment.

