### 2.4. Intervention: The Binaural Beats Intervention Program

BB is delivered through an auditory stimulus waveform that is interpreted as a brainwave pattern by the Reticular Activating System (RAS). The RAS regulates arousal, kinesiophobia, attention, and awareness—key elements of consciousness itself [73,74]. In this study, BB is layered with background music and will be provided in MP3 format following specific guidance, in the English language, based on fearless motion. All stimuli will be presented binaurally at High Beta and Gamma frequencies, via an auditory system incorporating headphones [75]. In fact, the purpose of High Beta and Gamma frequencies on athletes is to improve the athlete’s psychomotor and self-regulation ability, their confidence, and subsequent performance in important competitions [76]. The Binaural Beats (BB) intervention program will be designed and produced by the Monroe Institute (Faber, VA, USA).

This BB music-based intervention will be received in high beta and gamma frequencies (30–100 Hertz) at 30 bpm (slow tempo), 60 bpm (normal tempo), and 100 bpm (fast tempo). The binaural beat stimuli will consist of mixed sinusoidal tones producing frequency patterns will crop in length to a duration of six times intervals (total 15 min): 0–2 min the slow tempo (Grounding), 3 min (2–5 min) the slow tempo (Relaxation/Intention Setting), 3 min (5–8 min) the normal tempo (Imagery Begins), 2.5 min (8–10.5 min) normal tempo (Emotional Processing + Imagery/Movement), 2.5 min (10.5–13 min) fast tempo (Active Visualization + Affirmation), and 2 min (13–16 min) fast tempo (Return to Awareness, Light Activation) enabling athletes to hear the music; this duration will also be likely to yield more pronounced emotional response [77].

The intensity will be modified at approximately the isochrone tones to 14–16 dB.

Each athlete will receive the musical intervention via the website binaukine.com, which has been specifically designed by the researchers exclusively for the purposes of the present study. Furthermore, participants’ compliance with the study protocol will be monitored by the researchers through the frequency of the athletes’ visits to the website.

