The BB music-based intervention will be performed prior to each training session or competition, as part of the athletes’ warm-up routine. Athletes will be instructed to conduct the listening sessions in a quiet environment, seated comfortably with their eyes closed, and to avoid distractions from external stimuli during the intervention. All groups will receive the BB music-based interventions for 20 sessions, lasting 15 min per session, 5 times per week, over a period of 4 weeks.

Before beginning the BB music-based intervention phase, all athletes will attend a familiarization session during which the researchers will provide detailed instructions on how to perform the intervention. During the main intervention phase, the first session will be supervised by the research team, while the remaining sessions will be carried out individually, at different times according to each athlete’s training schedule. Each group will randomly receive the BB music-based intervention program.

The intervention group will receive a complete BB music-based intervention program. The placebo group will receive the same music-based intervention program with the verbal guidance but without the binaural beats. The control group will listen only to the music track, with the same music background as the intervention and placebo groups.

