## 5. Strengths and Limitations

A major strength of the present study is its double-blind randomized controlled trial design, which minimizes selection and assessment bias and enhances methodological rigor. The inclusion of experimental, placebo, and control groups allows the specific effects of binaural beats to be examined beyond the potential effects of music exposure and verbal guidance alone. In addition, the simultaneous evaluation of psychological outcomes, ANS function, handgrip strength, cardiovascular regulation (HRV), and fitness biomarkers provides a comprehensive biopsychophysiological assessment of professional athletes in open skill sports with chronic MSK-I. The inclusion of follow-up measurements four weeks after completion of the intervention further enables the examination of short-term maintenance effects.

Another strength of the study is the standardization of the intervention protocol. The binaural beats music-based intervention will be administered through headphones to ensure accurate binaural auditory stimulation. Furthermore, intervention duration, listening frequency, warm-up integration, auditory guidance, and environmental instructions will be standardized across participants to reduce variability in auditory exposure and improve intervention fidelity. The use of validated questionnaires and standardized physiological and functional assessment procedures further strengthens the reliability of the outcome measures and the internal validity of this study.

Nevertheless, several limitations should be acknowledged. First, participants will be recruited from collaborating sports clubs within the Attica region, Greece, which may introduce selection bias and limit the generalizability of the findings to athletes from other geographical regions, competitive levels, or sporting disciplines. Second, the study focuses exclusively on chronic lower-limb MSK-I, restricting the applicability of the findings to acute injuries, upper-limb musculoskeletal conditions, or post-surgical populations.

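### Participant blinding is claimed for all three arms, but the control track lacks the spoken guidance the other two arms hear, so the claim is secured only for experimental versus placebo

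*Protocol article*

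**What the plan says.** The blinding statement in section 2.1 makes no exception by arm: "Participants, outcome assessors, and statisticians will remain blinded to group allocation throughout the study". Section 2.2 repeats the label ("This double-blind randomized controlled trial will investigate the effects of binaural beats on biopsychological outcomes"), section 6 uses it again, and section 5 offers it as a safeguard: "A major strength of the present study is its double-blind randomized controlled trial design, which minimizes selection and assessment bias".

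The content of the arms is set out in the Abstract and section 2.4:

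- Experimental: "The intervention group will listen to BB embedded in music at high beta and gamma frequencies (30–100 Hz) with guided instructions".
- Placebo: "The placebo group will receive the same music-based intervention program with the verbal guidance but without the binaural beats".
- Control: "The control group will listen only to the music track, with the same music background as the intervention and placebo groups".

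Section 2.4 describes the recording as "following specific guidance, in the English language, based on fearless motion", and labels its segments with terms such as grounding, imagery, emotional processing and affirmation.

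On what athletes learn beforehand, section 2.2 says that "athletes will receive detailed oral and written information regarding the study aims and assessment procedures". Section 2.4 adds a familiarisation session and a first session supervised by the research team. The limitations in section 5 do not mention blinding.

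**The concern.** The experimental and placebo tracks differ only in the beats, so an athlete in either arm has no obvious cue. The control track differs from both in something anyone can hear: nobody speaks. An athlete who knows or learns that other tracks contain spoken guidance can work out that he or she is in the control arm. The article describes no step that hides this difference.

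TSK-17 is a self-report, and the theme of the guidance is close to what it measures. SCAT and PBPI are also self-reports. Maximal grip and the treadmill test to exhaustion depend on effort. On such measures a difference from control could come partly from knowing or suspecting that one received music only.

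Section 2.5 tests Group, Time and their interaction across all three arms. A significant overall result could therefore come from the control arm alone. If it were reported as a double-blind finding about binaural beats, the evidence would be overstated.

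**Working it through.** **1. What each arm hears (Abstract and section 2.4).**

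| Arm | Music | Spoken guidance | Binaural beats |
|---|---|---|---|
| Experimental | yes | yes | yes |
| Placebo | yes | yes | no |
| Control | yes | no | no |

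**2. What each contrast estimates.**

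| Contrast | Differs in | Spoken guidance matched? |
|---|---|---|
| Experimental vs placebo | beats | yes |
| Experimental vs control | beats + guidance (+ possible expectation) | no |
| Placebo vs control | guidance (+ possible expectation) | no |

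Two of the three contrasts involve the control arm. With 18 athletes per group (section 2.1), the arm is 18/54, or one third of the sample.

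**3. Illustration of scale.** The plan gives no figure to reproduce here, and the documents give no size for an expectation shift. I assume a pure shift d, in SD units, between control and a comparator, with no true effect. The test is a two-sided two-sample t-test with n per arm:

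- degrees of freedom = 2n − 2 = 34 for n = 18
- noncentrality = d × √(n/2) = d × √9 = 3d, which is 0.6, 0.9 and 1.5 for d = 0.2, 0.3 and 0.5
- rejection probability = P(|T| > c), where T is noncentral t and c is the critical value
- c = 2.032 at 0.05, and 2.518 at 0.05/3 = 0.0167 (Bonferroni over three contrasts)

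| Assumed d | Unadjusted, level 5% | Bonferroni, level 1.67% |
|---|---|---|
| 0.2 | 9.0% | 3.6% |
| 0.3 | 14.1% | 6.3% |
| 0.5 | 30.8% | 16.9% |

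With 16 per arm (the 48 athletes that section 2.1 gives as the minimum, divided by three), the same steps give 8.5%, 13.0% and 27.8% unadjusted, and 3.3%, 5.7% and 14.8% with Bonferroni.

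Section 2.5 plans pairwise comparisons with an adjustment for multiplicity but does not name the method, so the Bonferroni column is closer to what is planned. Each column should be read against its own nominal level. For d = 0.2, 3.6% is below 5% but about twice the 1.67% that applies to it.

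**4. One related statement.** Section 5 lists auditory guidance among the features standardised across participants. By section 2.4 the control arm receives none, so this is true of two arms at most.

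**The case against.** The strongest reply is that an athlete hears only one track. Music without speech reveals the allocation only to someone who knows what the other arms contain. Section 2.2 says athletes are told the aims and the assessment procedures, not the make-up of the arms, and the consent material is not shown. A control athlete may believe that beats are hidden in the music. After the first session, listening is individual and at different times, so comparison between teammates is possible but not shown. All of this stands. A reader might infer that the blind must fail and that control athletes will recognise their arm within the first minute; the documents do not support that. They do not say when speech begins or how the arms are described. What they show is that nothing in the design secures the blind for this arm.

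A reader might also infer that the control contrasts are unblinded altogether. That goes too far: nothing contradicts the blinding of outcome assessors and statisticians, and the suggestion that athletes would tell assessors is conjecture.

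It is also fair that SSR and HRV, the other two primary outcomes, are recorded by instrument and are less open to expectation. A music-only arm is a legitimate component comparator, and the contrast that isolates the beats is sound on this point. Finally, the section 5 sentence on guidance could be read as meaning identical guidance wherever it is given; even so, it needs a qualifier.

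What remains is that section 2.1 makes an unqualified claim, section 5 presents it as a major strength, and section 2.4 does not support it for one arm.

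**Conclusion.** The point holds in a limited form. Participant blinding is credible by design for experimental versus placebo and is not secured for the control arm: 18 of 54 athletes and 2 of 3 pairwise contrasts. The consequence falls mainly on TSK-17, SCAT, PBPI and the effort-dependent tests. It also reaches the overall group tests, because they include the control arm.

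The percentages above show scale only. They rest on an assumed shift, no true effect, a simple two-group test and 18 (or 16) per arm; they do not estimate the bias in this trial. The conclusion itself rests only on the comparison of sections 2.1, 2.2, 5 and 6 with section 2.4.

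It deserves correction before results are known, because it determines which contrast can support a claim about binaural beats.

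**What to change.** 1. In sections 2.1, 2.2, 5 and 6, limit the participant-blinding claim to experimental versus placebo, and keep the statement on assessors and statisticians. Name experimental versus placebo as the contrast that supports any claim about binaural beats. State that contrasts with control are not securely participant-blinded and reflect guidance plus possible expectation, and also the beats for experimental versus control. List this among the limitations, and correct the section 5 sentence on standardised auditory guidance.
2. In the participant information and the familiarisation session, describe the arms neutrally, for example as three audio programmes without listing their components. Ask athletes not to discuss their track with teammates or assessors. If the consent material already does this, a sentence in the article saying so is enough.
3. Optionally, add one item asking athletes to guess their arm, and report it by arm. Ask it after all outcome measures are complete, preferably at the last visit, because asking earlier could prime the TSK-17 answers.

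The cost is wording in the protocol and information sheet, plus at most one question. The arms, sample size and assessments stay as they are. The downside is a weaker stated claim for the comparisons with control.

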### 2.2. Procedures

This double-blind randomized controlled trial will investigate the effects of binaural beats on biopsychological outcomes in professional athletes with a history of chronic lower-limb musculoskeletal injuries. The study will be conducted in three phases: baseline (pre-intervention), immediately after the four-week intervention, and four weeks after completion of the intervention. Outcome measures will include self-report questionnaires assessing kinesiophobia, sport-related anxiety, and pain beliefs; physiological assessments of autonomic nervous system (ANS) function; handgrip strength; and fitness-related biomarkers, including maximal oxygen uptake (VO_2_max), blood lactate concentration, and heart rate variability (HRV). All athletes will complete a four-week standardized binaural beats music-based intervention incorporated into the warm-up phase prior to each training session and official game. The BB intervention will be administered 5 times per week (pre-training and pre-game), resulting in a total of 20 sessions. Each session will consist of 15 min of music listening (Figure 1).

Prior to initiating the intervention, athletes will receive detailed oral and written information regarding the study aims and assessment procedures from licensed physiotherapists with five years of clinical research experience. Data collection will include both subjective and objective measures and will be conducted at three time points: baseline (pre-intervention), immediately post-intervention, and four weeks after the completion of the intervention. Written informed consent will be obtained from all participants before enrollment.

### 2.3. Main Outcome Measures

All questionnaires will be administered in three phases: baseline (pre-intervention), immediately after the four-week intervention, and four weeks after completion of the intervention for all three groups. The questionnaires will assess kinesiophobia, sport-related anxiety, and pain-related beliefs. Final questionnaire scores will be used for statistical analysis, and predefined scoring criteria will be applied where relevant to characterize participants’ baseline psychological status.

#### 2.3.1. Tampa Scale of Kinesiophobia Questionnaire

The Tampa Scale of Kinesiophobia (TSK-17) is a self-report questionnaire designed to assess pain-related fear, which is considered a key component in the cognitive evaluation of musculoskeletal pain within the biopsychosocial model. The TSK consists of 17 items distributed across two dimensions: (i) activity avoidance, based on the belief that physical activity may lead to reinjury, and (ii) somatic focus [50,51]. Each item is rated on a 4-point Likert scale ranging from 1 (strongly disagree) to 4 (strongly agree). The total score is calculated after reversing the score (4 → 1) for items 4, 8, 12, and 16, resulting in a possible score range from 17 to 68 [52]. Total scores ≤ 37 indicate low levels of kinesiophobia, whereas scores > 37 indicate high levels [53]. The Greek version of the TSK-17 has been validated in the Greek population, demonstrating satisfactory internal consistency (Cronbach’s α = 0.74) and good test–retest reliability (ICC = 0.78) in individuals with chronic low back pain [54].

#### 2.3.2. Sport Competition Anxiety Test

The Sport Competition Anxiety Test (SCAT-15) is a self-report questionnaire designed to assess competitive anxiety in athletes [55]. The SCAT consists of 15 items related to various psychological factors such as anxiety, concentration and decision-making in training or competition settings [56]. Each item is rated on a 3-point Likert scale ranging from 1 to 3. The total score ranges between 10 and 30 points. Scores below 17 indicate a low level of competitive anxiety, scores between 17 and 24 indicate a moderate level of competitive anxiety, while scores above 24 indicate a high level of competitive anxiety. The Greek version of the SCAT-15 has been validated in the Greek population, demonstrating high internal consistency (Cronbach’s α = 0.85–0.87) and test–retest reliability (ICC = 0.84–0.89) [57].

